### Sampling

The study design uses only nasal samples for MRSA screening, for several reasons. Firstly, and most importantly, at the start of the study all published work evaluating the IDI-MRSA assay had used only nasal samples [11]. Secondly a nasal sample is easily obtainable for large scale screening, ensuring comprehensive coverage. Additionally, in previous studies nasal samples have been shown to have a high sensitivity (84%) [16]. Screening swabs are taken from all patients on admission and then if the sample is negative the patient is screened every four days until discharge, and upon the day of discharge. Regular sampling at 4 daily intervals enables the implementation of infection control procedures in a timely manner and the detection of cross infection. Additional samples, for example blood cultures and wound swabs are sent on clinical suspicion as is normal hospital policy.

All samples from the molecular wards are collected by a research nurse at 8 am and 2 pm, Monday to Friday and once daily at 1 pm on a Saturday and Sunday. Samples from the technical wards are transported to the laboratory using the hospital portering service which operates during the day 7 days a week.

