**Methods/Design:**

The study is a prospective two-period cross-over study set in 7 surgical wards covering different surgical specialities. A total of 10,000 patients > 18 years will be tested over 16 months. The only difference between the two study periods is the method used for the detection of MRSA in each ward (rapid v conventional culture), with all other infection control practices remaining consistent between the arms. The study has been designed to complement routine practice in the NHS. Outcomes are MRSA cross-infection rates (primary outcome) and need for antibiotic therapy and MRSA-related morbidity. Parallel economic and modelling studies are being conducted to aid in the interpretation of the results and to evaluate the cost-effectiveness of the rapid PCR screening strategy.

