### Overall study design and approach

The study is being carried out as a prospective cluster randomised two-period cross over study. A cross over study design allows a more rigorous means of measuring effectiveness than a simple prospective comparative study between wards. The only difference between the two study periods is the method used for the detection of MRSA in each ward, all other infection control practices are consistent between the wards. The aim of the study is to compare: (i) 'molecular' wards: patients are screened using the rapid IDI-MRSA test; and (ii) 'technical' wards: patients are screened using conventional culture. Results from the IDI_MRSA test are fed back within 2 hours of receipt of the samples to the molecular wards and within 2 days to the technical wards. One study arm contains 4 wards (Wards A), general surgery (1), trauma and orthopaedic (1), ENT (1) and thoracics (1), whilst the other arm contains 3 wards (Wards B), general surgery (1), trauma and orthopaedics (1) and urology (1). In the first period of the cross-over design, wards A were assigned to the molecular group and wards B to the technical group, with the assignment reversed for the second period.

Prior to commencement, educational sessions were held and information leaflets provided to all health care professionals working within the surgical directorate to provide them with information about the study and emphasise the importance of the work. Patient information leaflets, designed to ensure individuals are aware of necessary procedures for themselves, staff and visitors are provided.

Ethical approval was received from East Birmingham Ethics Committee. Written consent from study participants is not required as screening patients for MRSA is hospital policy. An initial two month pilot period was used to allow resolution of all operational and technical problems. This was followed by two 8 month cross-over periods, with one month follow up of study patients at the end of the final period. Wards A were allocated to the molecular arm of the study in the first period and Wards B to the technical arm.

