### Laboratory protocols

The traditional method for the identification of MRSA is by culturing swabs directly onto agar plates. A recent review has concluded that use of Baird-Parker containing ciprofloxacin agar plate without broth pre-enrichment is the most cost effective screening strategy [7]. However, due to the recent emergence of ciprofloxacin sensitive community MRSA strains, we have chosen not to use this method [17]. Furthermore, since this publication several chromogenic agars have been developed which offer a high degree of sensitivity and specificity [18]. Therefore the methodology chosen was to use direct inoculation onto MRSA ID, a chromogenic media, (Biomerieux, Marcy l'Etoile, France), followed by confirmation using DNase and slide agglutination tests (Oxoid, Basingstoke, UK) for identification of *Staphylococcus aureus *followed by full sensitivity testing using BSAC methods [19].

The samples from the molecular wards are always received in batches; on week days two batches of samples are received, one at 8 am and another at 2 pm, whilst at the weekend only one batch is processed. On receipt of the samples all swabs are immediately inoculated directly onto chromogenic media and then using the same swabs the DNA is extracted using the BD GeneOhm protocol. The primers and molecular beacons used are supplied by the manufacturer (Becton Dickinson, NJ, USA) and the real time amplification of DNA is run on Smartcyclers™ (Cepheid, CA, USA). All agar plates are read after overnight incubation, and confirmed using DNase and slide agglutination followed by full sensitivity testing using BSAC methods [19].

In cases of discrepant results between the PCR and culture, all direct culture plates are incubated for an additional 24 h before being reported as negative. Additionally all swabs which are positive by the PCR method are placed in brain heart infusion broth (Oxoid, Basingstoke, UK) on the day the PCR is completed, incubated overnight, sub-cultured onto chromogenic agar and confirmed as above. This additional step was added because it is known that although direct culture is the preferred method of detecting MRSA for operational reasons in the UK i.e. due to cost and time implications, it is not the most sensitive.

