Swabs from the technical wards are processed throughout the day, Monday to Friday and on Saturday mornings. The swabs are inoculated directly onto chromogenic agar and confirmed as previously described. All MRSA isolates, from both the technical and molecular wards are saved on protect beads and stored at -80C. The first isolate from each patient is epidemiologically typed using staphylococcal interspersed repeat unit (SIRU) typing as previously described and all results entered into Bionumerics™ [20].

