### Sample size

Given the limitations on published data available to inform the sample size estimate at the outset of the study, it was decided, in the light of operational constraints, to monitor MRSA colonisation and infection rates in seven wards for eighteen months, with a cross-over from molecular to technical testing or vice versa after nine months. Admission rates to the wards led to an estimated total of 10,000 patients being included in the study, with 5000 being assigned to each of the two periods.

Assuming that 5% of patients are MRSA colonised on admission to the wards, with a transmission rate in the technical wards of 0.5, a total of 125 new cases of infection in the control arm would be expected.

The power of the study can be calculated assuming that the number of new cases follows a Poisson distribution and using the normal approximation to the Poisson. If, for the purpose of the power calculation, it is assumed that admission rates and MRSA colonisation rates on admission are the same for all seven wards and in both periods, and that and MRSA transmission rates are the same for all wards using molecular or technical testing, a total of 10,000 admitted patients would mean that the study had 90% power to detect a reduction in the transmission rate from 0.5 to 0.3, corresponding to a drop in the expected number of new cases in the molecular wards from 125 to 75.

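### New cases are detected by the test under comparison, and only molecular-ward swabs can get extra culture steps, so detection of the primary outcome differs by arm

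*Protocol article*

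**What the plan says.** All references are to the protocol article.

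- **Outcome.** The abstract names cross-infection rates as the primary outcome. Data analyses models the number of new MRSA cases per ward and period as Poisson. Neither that section nor Sample size says which test makes a case.
- **Detection.** Sampling states: "Regular sampling at 4 daily intervals enables the implementation of infection control procedures in a timely manner and the detection of cross infection". Repeat screening depends on the previous result: "if the sample is negative the patient is screened every four days until discharge, and upon the day of discharge".
- **Test by arm.** Under Overall study design and approach, "molecular' wards: patients are screened using the rapid IDI-MRSA test", while technical wards use conventional culture.
- **Laboratory steps, molecular wards.** Every swab is plated on chromogenic agar before DNA extraction, and plates are read after overnight incubation. If PCR and culture disagree, the plate has a further 24 h. "Additionally all swabs which are positive by the PCR method are placed in brain heart infusion broth", then sub-cultured. The stated reason is that direct culture is not the most sensitive method; the Background says that broth improves sensitivity.
- **Laboratory steps, technical wards.** "The swabs are inoculated directly onto chromogenic agar and confirmed as previously described". No PCR or broth step is described.
- **Typing.** The first isolate from each patient is SIRU-typed in both arms.
- **Planning figures.** "Assuming that 5% of patients are MRSA colonised on admission to the wards, with a transmission rate in the technical wards of 0.5" gives 125 expected new cases in the control arm, against 75 under the target effect.

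**The concern.** A new case has to be told apart from a carrier who was already positive on admission. Both classifications rest on screening swabs, and the two arms read those swabs differently. Two mechanisms pull in opposite directions:

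- A more sensitive procedure finds more true acquisitions, which raises the molecular count.
- It also leaves fewer admission carriers undetected. A missed carrier who tests positive later looks like a new case, so this mechanism raises the technical count.

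Counting only culture-positive patients does not by itself equalise the arms, because extended incubation and broth are triggered by a PCR result and so exist only on molecular wards. The cross-over does not help either: when a ward switches arm, its detection procedure switches too, and the within-ward contrast carries the whole measurement difference. An observed effect, or its absence, could then partly reflect detection rather than transmission.

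**Working it through.** **1. The plan's own figures.** Sample size gives 5,000 patients per period (taken here as 5,000 per testing arm), 5% colonised on admission, and transmission rates of 0.5 and 0.3.

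- Admission carriers: 5,000 × 0.05 = 250 per arm.
- New cases: 250 × 0.5 = 125 and 250 × 0.3 = 75, as stated.
- Power = Φ((125 − 75)/SE − 1.96), assuming two-sided 5%. With SE = √(2 × 125) = 15.8 it is 88.5%; with SE = √(125 + 75) = 14.1 it is 94.2%. The stated 90% is consistent with this.

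The calculation has no term for imperfect or unequal detection.

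**2. Adding detection, with no true effect.** Let s be per-swab sensitivity and r the chance that a carrier missed on admission is positive later. With perfect specificity:

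observed new cases = 125s + 250(1 − s)r

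Molecular s = 0.917 comes from the Background. Technical s is an assumption, varied from 0.70 to 0.85. The 84% in Sampling concerns the nasal site, not the culture method. Two extremes are taken: r = 0 (missed carriers never found) and r = s (one later retest, with any positive counted as new).

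Molecular arm: r = 0 gives 125 × 0.917 = 114.6; r = s gives 114.6 + 250 × 0.083 × 0.917 = 133.7.

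| Technical s | Technical cases, r = 0 | Ratio mol./tech. | Technical cases, r = s | Ratio mol./tech. |
|---|---|---|---|---|
| 0.85 | 106.2 | 1.08 | 138.1 | 0.97 |
| 0.80 | 100.0 | 1.15 | 140.0 | 0.955 |
| 0.70 | 87.5 | 1.31 | 140.0 | 0.955 |

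The true ratio is 1.00 throughout. With r = 0, the chance of a significant result against PCR is 8%, 17% and 48%, instead of 2.5% (two-sided 5%, Poisson, SE = √(sum of counts)).

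**3. The planned effect (125 to 75), r = 0.** Molecular cases are 75 × 0.917 = 68.8. The ratio becomes 0.65, 0.69 and 0.79 instead of 0.60, and power is 81%, 67% and 32%, against 92% if both arms had sensitivity 0.917.

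**4. Whether a common plate definition is enough.** Suppose cases are defined by the plate in both arms, but PCR-positive/plate-negative patients, who exist only on molecular wards, are censored. Take plate sensitivity 0.80, PCR 0.917, no true effect, and PCR positive whenever the plate is:

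- Technical: 125 × 0.80 + 250 × 0.20 × 0.80 = 140.
- Molecular: 125 × 0.80 + 250 × 0.083 × 0.80 = 116.6.
- Ratio: 116.6/140 = 0.83.

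One-sided censoring thus creates an apparent 17% reduction in counts. The patients behind it are the 250 × (0.917 − 0.80) = 29.25 admission carriers removed in one arm only. Counting none of them as later cases gives 116.6; counting all gives 116.6 + 29.25 = 145.9. Weighting them by plate sensitivity gives 116.6 + 29.25 × 0.80 = 140, which restores equality. Bounds of this kind therefore bracket the right answer under these assumptions.

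**The case against.** The strongest reply is that the article never says a case is defined by whichever test the ward uses. Every swab in both arms goes onto chromogenic agar, isolates in both arms are typed, and the Discussion cites typing as the means of identifying transmission events. Broth and extended incubation may be there only for the accuracy comparison that is one of the study's aims. A full protocol or analysis plan may already fix a common definition.

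Much of this stands, and it rules out three stronger readings that a reader might infer:

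- **That PCR false positives count as cross-infections.** A 1% false-positive rate among 5,000 − 250 − 125 = 4,625 never-carriers would give about 46 false cases per follow-up swab, close to the 50-case target difference. But no text says that a PCR-only positive is a case, such a positive yields no isolate to type, and no PCR specificity is given.
- **That the bias is a 17% reduction per colonised admission.** At culture sensitivity 0.80 with r = s, 140/200 = 0.70 against 133.7/229 = 0.58. That divides by test-detected carriers, a ratio the article uses only for planning. On the case counts in the main model, the same scenario gives 133.7 against 140, about 4.5%.
- **That the bias favours PCR.** The table shows that it can go either way.

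What does not fall away is that the article assigns outcome detection to the screening swabs, describes unequal laboratory work on them by arm, and makes repeat screening depend on a negative result. Typing needs an isolate, so it does not correct an unequal search for isolates. The test accuracy to be estimated under Data analyses is not linked to the case count.

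**Conclusion.** The concern holds as a difference in detection of unknown size and direction. As described, admission carriage and new cases are ascertained by arm-dependent procedures, and the cross-over leaves that difference intact. Under the illustrative range (culture sensitivity 0.70 to 0.85, PCR 0.917, perfect specificity), the null ratio of new cases lies between about 0.955 and 1.31, depending mainly on whether missed admission carriers are later counted as new. The 0.955 end is small beside the targeted 40% reduction; the 1.31 end would hide much of it. These figures also assume Poisson counts without extra ward-level variation and at most one retest of each missed carrier. They show sensitivity to the definition and are not estimates of the actual bias. If a fuller document already sets a common case definition, stating it settles the definition, but the handling of missed admission carriers must still be shown to be the same in both arms.

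**What to change.** 1. **Common case definition.** For the primary analysis, define a new case in both arms by the direct chromogenic plate, read after the same overnight incubation and confirmed by DNase and slide agglutination. PCR-only, extended-incubation and broth-only positives go to a secondary analysis.
2. **Denominator.** Model new cases per admission or per patient-day at risk, counted in the same way in both arms, and not per test-detected admission carrier.
3. **Missed admission carriers.** Do not rely on censoring PCR-positive/plate-negative patients in the molecular arm alone. Handle missed carriers in the same way in both arms, with sensitivity analyses that:
   - (a) exclude, in both arms, cases first positive on the first follow-up swab;
   - (b) require a SIRU type matching another patient on the ward, using direct-plate isolates only, so that broth-only isolates do not re-enter through typing;
   - (c) bound the result by counting none, then all, of the PCR-positive/plate-negative patients as later cases, and use the planned accuracy estimates to judge where between the bounds the answer lies.

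**Cost.** No new samples or tests, since plating and typing are already planned in both arms. The primary analysis loses some events, namely those seen only by PCR, prolonged incubation or broth. Analysis (a) loses more, because with an average stay of 4 to 4.5 days many patients will have only one or two follow-up swabs; it should be read as a check and not as a replacement. The article describes recruitment as nearly complete, so the definition should be fixed and dated before outcome data are compared by arm.

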### Rapid communication of results to the wards

All results, both positive and negative, are made available on the laboratory reporting system to which all ward staff have access via a computerised reporting system, immediately upon completion of the test. In addition, all positive MRSA results, both rapid and conventional are telephoned to nurses on the wards, with the time and the person receiving the result documented.

### Laboratory protocols

The traditional method for the identification of MRSA is by culturing swabs directly onto agar plates. A recent review has concluded that use of Baird-Parker containing ciprofloxacin agar plate without broth pre-enrichment is the most cost effective screening strategy [7]. However, due to the recent emergence of ciprofloxacin sensitive community MRSA strains, we have chosen not to use this method [17]. Furthermore, since this publication several chromogenic agars have been developed which offer a high degree of sensitivity and specificity [18]. Therefore the methodology chosen was to use direct inoculation onto MRSA ID, a chromogenic media, (Biomerieux, Marcy l'Etoile, France), followed by confirmation using DNase and slide agglutination tests (Oxoid, Basingstoke, UK) for identification of *Staphylococcus aureus *followed by full sensitivity testing using BSAC methods [19].

The samples from the molecular wards are always received in batches; on week days two batches of samples are received, one at 8 am and another at 2 pm, whilst at the weekend only one batch is processed. On receipt of the samples all swabs are immediately inoculated directly onto chromogenic media and then using the same swabs the DNA is extracted using the BD GeneOhm protocol. The primers and molecular beacons used are supplied by the manufacturer (Becton Dickinson, NJ, USA) and the real time amplification of DNA is run on Smartcyclers™ (Cepheid, CA, USA). All agar plates are read after overnight incubation, and confirmed using DNase and slide agglutination followed by full sensitivity testing using BSAC methods [19].

In cases of discrepant results between the PCR and culture, all direct culture plates are incubated for an additional 24 h before being reported as negative. Additionally all swabs which are positive by the PCR method are placed in brain heart infusion broth (Oxoid, Basingstoke, UK) on the day the PCR is completed, incubated overnight, sub-cultured onto chromogenic agar and confirmed as above. This additional step was added because it is known that although direct culture is the preferred method of detecting MRSA for operational reasons in the UK i.e. due to cost and time implications, it is not the most sensitive.

Swabs from the technical wards are processed throughout the day, Monday to Friday and on Saturday mornings. The swabs are inoculated directly onto chromogenic agar and confirmed as previously described. All MRSA isolates, from both the technical and molecular wards are saved on protect beads and stored at -80C. The first isolate from each patient is epidemiologically typed using staphylococcal interspersed repeat unit (SIRU) typing as previously described and all results entered into Bionumerics™ [20].

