### Data collection

A comprehensive data set is being collected on all study patients. Data is entered directly by the research nurses onto laptops on the wards using a specifically modified Access database and then uploaded onto a secure server. Information collected includes patient ID, demographic data, risk factors, antibiotic usage, bed movements, length of stay, and treatment outcomes. For patients who are colonised with MRSA additional information is collected regarding implementation of infection control measures and decolonisation treatment.

Laboratory data collated includes patient ID, date and time sample taken and received by lab, and the IDI_MRSA and culture results.

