### Data analyses

Analysis will be based on all individuals presenting for admission to the 7 surgical wards (intention to treat), including emergency and planned admissions. Numerical and graphical summaries of all the data will be compiled, including a detailed description of missing data at the ward and individual level.

Sensitivity and specificity will be estimated for PCR and culture tests. Receiver operating characteristic (ROC) curves are not appropriate because this is not a quantitative test. However, the positive predictive value (PPV) and negative predictive value (NPV) will be calculated. We will examine test replicability (i.e. precision) which reflects the variance in a test result that occurs when the test is repeated on the same specimen. Test reliability (e.g. failure rates) and laboratory turn-around time will also be compared.

The main clinical outcome measures will be MRSA cross-transmission rates, antibiotic therapy and MRSA-related morbidity. Secondary outcome measures will include length of in-patient stay, ITU episodes, a final outcome recorded at discharge, and MRSA infection at the outpatient follow-up clinic. Measures of resource use will include the cost of hospital episode and any re-admissions for MRSA.

The numbers of patients becoming infected, the cross-transmission rates and the numbers of MRSA-related deaths within each ward will be compared for the molecular and technical periods. The main analysis will focus on ward by period level data summaries. It seems likely that the number of new MRSA cases observed in each ward in each period will follow a Poisson distribution with mean depending on the size and type of the ward and whether the molecular or technical testing is being used in that period. A non-linear repeated measures random-effects analysis will be used to compare the mean number of cases, rate of cross-infection and number of MRSA related deaths. Ward by period interaction-level covariates could be included in this analysis. Depending on the observed rate of MRSA colonisation or infection and admission to the different wards, a normal approximation to the Poisson distribution may be appropriate, enabling linear modelling techniques to be used.

Further analyses will use linear or non-linear mixed effect models to assess the effects patient-level covariates. Estimates of the difference between the molecular and technical periods adjusted for the effect of covariates will be obtained.

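### Follow-up culture is triggered by the PCR result, so sensitivity of both PCR and direct culture is overstated if those results enter the reference

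*Protocol article*

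**What the plan says.** All statements are in the Protocol article.

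- **Culture and PCR on every molecular-ward swab (Laboratory protocols):** "On receipt of the samples all swabs are immediately inoculated directly onto chromogenic media and then using the same swabs the DNA is extracted". Plates are read after overnight incubation.
- **Extra incubation:** "In cases of discrepant results between the PCR and culture, all direct culture plates are incubated for an additional 24 h". This happens before a plate is reported as negative.
- **Broth enrichment:** "Additionally all swabs which are positive by the PCR method are placed in brain heart infusion broth". The reason given is that direct culture is preferred on operational grounds but "it is not the most sensitive".
- **Technical wards:** "The swabs are inoculated directly onto chromogenic agar and confirmed as previously described". No PCR or broth is described there, so paired PCR and culture results come only from wards in their molecular period.
- **Planned estimates (Data analyses):** "Sensitivity and specificity will be estimated for PCR and culture tests", with positive and negative predictive values. The section names no reference standard.
- **Recorded laboratory results (Data collection):** besides identifiers and sample times, "and the IDI_MRSA and culture results". No third, independent test is described.
- **Repeat sampling (Sampling):** patients who test negative are swabbed again every four days and on the day of discharge.

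**The concern.** How hard a swab is searched for MRSA depends on the test under evaluation. A plate-negative swab can become culture-positive only if PCR was positive. A swab negative on both tests has no further culture, so a carrier missed by both will always count as a true negative. The protocol itself accepts that the direct plate misses carriers, yet looks for the missed ones only among PCR positives. This is differential verification. It removes false negatives from view and raises apparent sensitivity for both tests.

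Culture raises a second problem. With only PCR and culture recorded, any conventional reference would contain culture. If every culture-positive swab counts as a true positive, culture specificity is 100% by construction. If the direct plate alone is the reference, culture sensitivity is 100% by construction. Neither figure is informative.

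At stake is what aim 2 can conclude about the rapid test against culture. Because negative patients are swabbed repeatedly, swabs are also not independent, and an analysis that treats them as independent would misstate precision.

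**Working it through.** The article gives no accuracy estimate or precision target of its own, so there is no figure to reproduce.

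**Which swabs can change status**

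| PCR | Overnight plate | Extra 24 h | Broth | Can culture status change? |
|---|---|---|---|---|
| + | + | no | yes | no, already positive |
| + | − | yes | yes | yes, to positive |
| − | + | yes (discrepant) | no | no, already positive |
| − | − | no | no | no, never searched |

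Only one cell can move, and it moves in PCR's favour.

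**Inputs.** The only PCR sensitivity in the article is 91.7% (Background, an early evaluation of 288 patients). Everything else is assumed: direct-plate sensitivity dc = 0.80, broth sensitivity br = 0.95, culture 100% specific, and PCR detecting a fraction pd of plate-positive and pn of plate-negative carriers. The extra 24 h is treated as adding nothing beyond broth.

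**Formulas (among true carriers)**

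- Chance that broth grows MRSA after a plate miss: b = (br − dc)/(1 − dc) = 0.15/0.20 = 0.75.
- Reference-positive with PCR-triggered broth: R = dc + (1 − dc)·pn·b.
- Confirmed PCR positives: P = dc·pd + (1 − dc)·pn·b.
- Apparent PCR sensitivity: P/R. With every swab enriched: P/br. Against the plate alone: pd.
- Apparent culture sensitivity: dc/R. With every swab enriched: dc/br = 0.80/0.95 = 84.2%.

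**Results**

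| (pd, pn) | R | P | PCR: plate alone | PCR: triggered broth | PCR: all enriched | Culture: triggered broth |
|---|---|---|---|---|---|---|
| A (0.97, 0.50) | 0.8750 | 0.8510 | 97.0% | 97.3% | 89.6% | 91.4% |
| B (0.95, 0.30) | 0.8450 | 0.8050 | 95.0% | 95.3% | 84.7% | 94.7% |
| C (0.917, 0.917) | 0.9376 | 0.8712 | 91.7% | 92.9% | 91.7% | 85.3% |

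- **Triggered broth minus plate alone:** 0.3, 0.3 and 1.2 points. This is what selective follow-up itself adds.
- **Triggered broth minus all enriched:** 7.7, 10.5 and 1.2 points. In A and B nearly all of this gap is already present with the plate alone, because PCR and plate miss the same carriers.
- **Culture, triggered broth minus all enriched (84.2%):** 7.2 points in A, 10.5 in B and 1.1 in C.

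**Wider assumptions.** A second model varied plate sensitivity from 60% to 90% and broth recovery after a plate miss from 80% to 100%. It let PCR and culture errors be independent or correlated at half the maximum covariance.

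| True PCR sensitivity | Errors | Triggered broth | Plate alone |
|---|---|---|---|
| 91.7% | independent | 92.3–94.8% | 91.7% |
| 91.7% | correlated | 96.0–97.4% | 95.8–95.9% |
| 80% (assumed) | independent | 81.3–87.0% | 80.0% |
| 80% (assumed) | correlated | 85.0–93.0% | 84.4–90.0% |

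Direct-culture sensitivity is overstated by about 1 to 14 points. At an assumed true PCR specificity of 97% and the article's 5% prevalence, apparent PCR specificity is 96.6–97.0% with triggered broth and 95.2–96.8% against the plate alone.

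**A comparison that survives.** The ratio of confirmed positives found by PCR to those found by the overnight plate is P/dc: 0.8510/0.80 = 1.064 in A, 1.006 in B and 1.089 in C. The denominator R (or br) cancels, so each ratio is the same as if every swab had been enriched.

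**The case against.** The strongest reply is that the plan never says the broth or extended-incubation results enter the reference. Laboratory protocols describes bench procedure, and a condensed article may leave the reference standard and unit of analysis to the full protocol or analysis plan. That stands: the missing definition is not itself an error, and a reader who infers that the planned estimates are certainly biased by the triggered results goes beyond the text. The workflow, however, is fixed here. On the procedures described, no later analysis plan can supply enriched results for swabs negative on both tests. Nor does ignoring broth remove the dependence, because the reporting rule "all direct culture plates are incubated for an additional 24 h before being reported as negative" makes the reported culture result itself depend on PCR.

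A second reply is that the large figures have another cause. This also stands. A reader might attribute the whole 1 to 11 points to selective follow-up, or expect a plate-only comparison to cure the bias. The working supports neither: in A and B the plate alone gives 97.0% and 95.0%, almost as far above 89.6% and 84.7%.

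Third, all inputs except 91.7% are assumptions, and with that figure and no dependence on load (C) the effect is about one point. That too is correct.

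Finally, a reader might suppose that the transmission model relies on these accuracy figures. The Modelling section mentions the literature and data from the primary research, not accuracy estimates.

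**Conclusion.** The concern holds in conditional form. Follow-up culture depends on the test being evaluated, and carriers negative on both tests are never sought. If the PCR-triggered results enter the reference, absolute sensitivity is overstated for both PCR and direct culture.

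With plate 80% and broth 95% assumed, selective follow-up adds about 0.3 to 1.2 points to PCR sensitivity relative to the plate alone. The addition is larger in parts of the wider grid: up to 7.0 points if PCR finds 80% of carriers, the plate finds 60% and errors are independent. Against full enrichment the PCR gap is about 1 to 11 points. Its upper end rests on the assumption that PCR and plate miss the same low-load carriers. Direction was the same in every scenario tried; size depends on figures the article does not give.

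Absolute sensitivity cannot be recovered without bias from either reference unless PCR and plate errors are assumed independent, which these data cannot test. The point concerns aim 2. The ward-level analysis of cross-transmission does not use these estimates.

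**What to change.** Change the accuracy analysis as follows.

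1. **Primary:** compare PCR with the overnight direct-plate reading on all molecular-ward swabs, and report positive and negative agreement rather than sensitivity and specificity.
2. **Separate discrepant-resolved analysis:** show the extended-incubation and broth results here, with the direction of bias stated. Compare the tests by the ratio of confirmed positives each detects, which does not need double-negative swabs to be verified.
3. **Limits:** state that absolute sensitivity cannot be estimated without bias under either reference. Do not report culture sensitivity or specificity against a reference that contains culture.
4. **Unit of analysis:** use one admission swab per patient, or all swabs with patient-clustered standard errors.

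No new laboratory work is needed. The overnight reading must be kept separate from the final culture result; Data collection does not say whether both are stored, so this should be checked. The other cost is that apparent PCR specificity and PPV look lower against the single plate. For example, take scenario A with 5% prevalence and an assumed 97% specificity. PCR positives are 0.05 × 0.876 + 0.95 × 0.03 = 0.0723, where 0.876 = 0.80 × 0.97 + 0.20 × 0.50. Apparent PPV is then 0.05 × 0.776/0.0723 = 53.7% against the plate (0.776 = 0.80 × 0.97), compared with 0.05 × 0.851/0.0723 = 58.9% with triggered broth.
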